**LIST OF ABBREVIATIONS AND RELEVANT DEFINITIONS**

| **AE** | **Adverse Event** |
| --- | --- |
| **DSMB** | **Data Safety Monitoring Board** |
| **EU** | **European Union** |
| **GCP** | **Good Clinical Practice** |
| **IC** | **Informed Consent** |
| **METC** | **Medical research ethics committee (MREC); in Dutch: medisch ethische toetsing commissie (METC)** |
| **MIC** | **Minimal Clinical Important Change** |
| **MCID** | Minimal Clinically Important Difference |
| **POSAS** | **Patient and Observer Scar Assessment Scale** |
| **RCT** | **Randomized controlled trial** |
| **(S)AE** | **(Serious) Adverse Event** |
| **SPC** | **Summary of Product Characteristics (in Dutch: officiële productinfomatie IB1-tekst)** |
| **SPSS** | **Statistical Package for the Social Sciences** |
| **Sponsor** | **The sponsor is the party that commissions the organisation or performance of the research, for example a pharmaceutical**  **company, academic hospital, scientific organisation or investigator. A party that provides funding for a study but does not commission it is not regarded as the sponsor, but referred to as a subsidising party.** |
| **SUSAR** | **Suspected Unexpected Serious Adverse Reaction** |
| **TBSA** | **Total Body Surface Area** |
| **WMO** | **Medical Research Involving Human Subjects Act (in Dutch: Wet Medisch-wetenschappelijk Onderzoek met Mensen** |
|  |  |
|  |  |
|  |  |
|  |  |
|  |  |
|  |  |
|  |  |
|  |  |
|  |  |
|  |  |
|  |  |

**SUMMARY**

**Rationale:** Surgical debridement is an important step in the management of patients with deep dermal or full thickness burns. Its purpose is to remove necrotic and/or infectious tissue and to prepare the wound for definitive healing. Conventional surgical debridement of burn wounds prior to skin grafting commonly consists of sharp tangential excision of non-viable burn eschar with hand-held knives. This procedure is not only associated with substantial blood loss, but also with unnecessary removal of viable dermis. During the last decade, hydrosurgery has become popular in burn surgery as an alternative to sharp tangential. The Versajet™ hydrosurgery system (Smith and Nephew, St. Petersburg, FL, USA) was developed in 1997 for the purpose of debriding many types of wounds, including burn prior to skin grafting. This system uses a high-pressure jet of sterile physiological saline to debride wounds, drawing tissue debris and fluid into a chamber via the Venturi effect created by the saline jet. Using the cutting effect of the high-pressure jet of saline, tissue may theoretically be excised in a tangential manner with maximal dermal preservation. This preservation of dermal tissue, which might have been excised by conventional techniques, suggests that subsequent scarring might be reduced. Two randomised controlled trials compared conventional and hydrosurgical excision of burns^1,2^. However, although scar quality is considered to be one of the most important outcomes in burn surgery, these studies did not address scar quality as primary outcome. One retrospective study did compare scar quality as primary long term outcome, and reported a better scar quality after hydrosurgical excision in a subgroup (age 5 years and older) of their study population 1 year post surgery^3^. On the other hand, Hyland et al. (2007) reported no significant differences found between scarring at 3 or 6 months after-injury as a secondary outcome in a prospective RCT comparing conventional excision with hydrosurgical excision^2^. To evaluate the

added value of hydrosurgery, a prospective randomised clinical trial is needed.

**Objective**: To assess long term scar quality of deep dermal burns after debridement with hydrosurgical excision versus conventional tangential excision.

**Study design:** A multicentre intra-patient randomized controlled trial.

**Study population:** All burn patients admitted to one of the three Dutch burn centres with deep dermal burns of at least 50cm^2^ who require excision and grafting will be included. In total 105 patients will be recruited with a follow-up of 12 months post-surgery.

**Intervention:** Prior to surgery two intervention areas will be appointed, which are randomly allocated to either hydrosurgical- or conventional tangential excision. Peroperatively, two punch biopsies in each intervention area will be collected before and after excision to evaluate the debridement efficacy and to determine dermal preservation.

**Main study parameters/endpoints:** The main study parameter is scar quality 12 months post-surgery as assessed with the POSAS (Patient and Observer Scar Assessment Scale) scored independently by two blinded observers. In addition, we will compare other scar quality outcomes 3, 6, and 12 months post-surgery and dermal preservation after the two different kinds of surgery. Alongside the trial we will perform a clinimetric study into the Minimal Important Change of the POSAS. To this end we will document the global perceived effect of both excision techniques.

**Nature and extent of the burden and risks associated with participation, benefit and group relatedness:** Both treatments are applied in the Netherlands and considered standard treatment. Therefore, there is no additional risk or discomfort for the patient.

Two punch biopsies of both intervention areas will be collected before and after excision during surgery when the patient is sedated. In this trial we use the smallest punch biopsy with a diameter of 3 mm, so interference is limited e since a better scar quality is the aim of this study. As the assessment of scar outcomes by the Patient and Observer Scar Assessment Scale, Cutometer® and Dermaspectometer® test are all non-invasive measurements requiring limited registration time, the total duration of all measurements is estimated at 30 minutes per subject. No additional risks are to be expected. When possible, scar quality is assessed combined with a regular outpatient visit to the burn centre physician. If patients are willing to participate but unable to visit the outpatient department, the patient will be visited by members of the research team.

# INTRODUCTION AND RATIONALE

Surgical debridement is an important step in the treatment of burn patients. Its purpose is to remove necrotic and/or infectious tissue and to prepare the wound for definitive healing. Conventional surgical debridement of burn wounds prior to skin grafting commonly consists of sharp tangential excision of non-viable burn eschar with hand-held knives. This procedure is not only associated with substantial blood loss, but also with unnecessary removal of viable dermis^2,4-6^. During the last decade, hydrosurgery, a new alternative type of tangential excision, has become popular in burn surgery. The Versajet™ hydrosurgery system (Smith and Nephew, St. Petersburg, FL, USA) was developed in 1997 for the purpose of debriding many types of wounds, including burns prior to skin grafting. The Versajet II system was CE marked in 2011 and was launched in 2012^7^. The Versajet II™ system works by producing a high-pressure jet of water across an aperture in an angled handpiece. The Venturi effect creates a vacuum that removes surface debris, which is sucked into the machine together with the irrigation fluid. The cutting and aspiration effects can be controlled by adjusting console power settings, handpiece orientation, and handpiece pressure. Tissue may theoretically be excised in a tangential manner with maximal dermal preservation. This preservation of dermal tissue, which might have been excised by conventional techniques, suggests that subsequent scarring might be reduced.

Because burn specialists assume superior results when using hydrosurgery in the treatment of deep dermal burns, it is a widely accepted alternative for conventional tangential debridement.

In the last 6 years in Dutch burn care, each year around 750 patients were hospitalised in one of the three burn centres. Of this number approximately 40% needed surgical treatment for their burn injuries. In over 80% of the operations tangential excision was the preferred technique. In 40% of these operations hydrosurgery was used for tangential excision and conventional excision with a knife for the remaining 60%^8^. However, a limited amount of studies is available on the effects of hydrosurgery.

Several clinical studies described the efficacy and safety of the Versajet hydrosurgery apparatus as a wound debridement tool in paediatric and adult burns^5,9-13^. There are four known prospective randomised controlled trials published in the medical literature comparing Versajet™ with conventional debridement in acute and chronic wounds^1,2,14,15^.

Up to now, studies of Gravante et al. (2007) and Hyland et al. (2015) have been the only published randomised controlled trials that compared Versajet™ and conventional debridement in burn patients^1,2^. The conclusions of both studies were that there were no significant differences in healing time, contracture rates or post-operative pain between either treatment methods.

Although scar quality is considered to be one of the most important outcomes in burn surgery, both studies did not address scar quality as primary outcome.

Gravante et al. found a shorter time of debridement for difficult areas such as the face, hands and genitalia^1^. However, the overall operation duration was equivocal. They described that in all patients who were treated with the Versajet™ system adequate debridement of the wound bed was possible during surgery. They suggested that hydrosurgical tangential excision was more precise in obtaining the correct dermal plane following debridement. They did not confirm this with objective measurement tools and they had no follow-up of patients to report scar quality. Only Hyland et al. reported histological evidence to support a significant difference in the amount of viable dermal preservation between the two groups in favour of the hydrosurgical group^2^. As a secondary outcome Hyland et al. did not observe significant differences in short term scar quality measured with the Vancouver Scar Scale at 3 and 6 months. Unfortunately, this study did not objectively assess scarring. Also, data on long term follow-up were unavailable, which is essential as scars mature over a period of at least one year^16,17^. Nevertheless, a retrospective study conducted at the Burn Center of the Martini Hospital of Groningen did compare scar quality as primary long term outcome, using the observer score of the POSAS (Patient and Observer Scar Assessment Scale) which is a subjective assessment tool. They reported a better scar quality after hydrosurgical excision in a subgroup (age 5 years and older) of their study population^3^. To assess the importance of hydrosurgery on quality of burn scar outcome we want to conduct a prospective randomised clinical trial.

The primary objective of this study is to compare long term scar quality of deep dermal burns after debridement with hydrosurgical- and conventional tangential excision.

In this study, we will use several objective and subjective tools for standardized scar evaluation. General aspects of the scar are evaluated by the POSAS.

Our secondary objectives are 1) To compare dermal preservation following tangential excision either performed hydrosurgically or conventionally and 2) To determine the minimal clinical important (MIC) change of the Patient and Observer Scar Assessment Scale (POSAS). The POSAS has proven to be a reliable, feasible and valid scar assessment scale. As clinimetric development is ongoing, a value for the MIC (minimal important change) is still lacking. Without a MIC, it is not possible to translate POSAS scores into clinical important and relevant differences for patients^18,19^. Especially in this study, in which the expected differences in scar quality between the two excision techniques may be subtle, a MIC value is crucial for interpreting study results. For this reason, we will conduct a clinimetric sub study alongside this RCT to determine the MIC of the POSAS. Additionally, we will determine the MCID (Minimal clinically important difference) of the POSAS at final follow up. This is the minimal difference in scar quality that patients experience as important.

# OBJECTIVES

**Primary objective:**

- To assess superior long term scar quality of deep dermal burns after debridement with hydrosurgical versus conventional tangential excision.

**Secondary objectives:**

- To demonstrate increased dermal preservation in deep dermal burns after debridement with hydrosurgically versus conventional excision.
- To determine the minimal clinical important (MIC) change of the Patient and Observer Scar Assessment Scale (POSAS).

# STUDY DESIGN

This study will be a multicentre randomized intra-patient controlled trial with a study period of 3 years. The burn centers of the Red Cross hospital in Beverwijk, the Martini hospital in Groningen and the Maasstad hospital in Rotterdam will participate.

Patients treated in the burn centre of the Red Cross hospital, Martini hospital, and Maasstad hospital between 02/01/2017 and 01/07/2018

Patients excluded from prospective cohort:

- Burn wounds < 50cm^2^
- TBSA > 30%
- Full thickness burns
- Chemical or electrical burns
- Infected wounds
- Patients that are unlikely to comply with requirement of the study protocol and follow-up
- No informed consent

Patients eligible for trial

(Deep dermal burned and an indication for hydrosurgical or conventional tangential excision)

Study patients included

Debridement with hydrosurgery and conventional excision

Loss to follow-up

3 months follow-up

Scar measurements and questionnaires

Loss to follow-up

6 months follow-up

Scar measurements and questionnaires

Loss to follow-up

12 months follow-up

Scar measurements and questionnaires

# STUDY POPULATION

## Population (base)

All burn patients admitted to the Beverwijk, Groningen or Rotterdam Burn Centre with deep dermal burns who require excision and grafting.

## Inclusion criteria

- - - All ages
    - Deep dermal burns who require primary excision and grafting
    - Informed consent

## Exclusion criteria

- Burn wound areas <50 cm^2^
- Full thickness burns
- Chemical or electrical burns
- Infected wounds (clinical symptoms in combination with positive wound swabs)
- Insufficient knowledge of the Dutch or English language
- Patients that are unlikely to comply with requirement of the study protocol and follow-up

## Sample size calculation

Power calculation is based on the result obtained by Scholten et al.^3^ in their retrospective study on scar quality after hydrosurgery versus guarded knife excision.

The mean POSAS Observer Score in the hydrosurgery was 14.7 versus 16.7 in the guarded knife group 12 months post-surgery, with a pooled SD of 6.53, resulting in an effect size of 0.3. Because of the within-subject design, a correction for correlated samples was included, assuming a correlation of 0.4 between POSAS Observer Score within one patient. Given a power of 0.8 and a level of significance of 0.05 a number of 105 patients is needed. Because our primary outcome is not assessed until one year post-surgery we anticipate on a drop out of 30%, which means we will include 137 patients.

Annually approximately 750 patients are admitted to one of the three Dutch burn centres. From these patients approximately 300 will require a surgical intervention of which 240 consists of tangential excision. We expect that the majority of these patients, but at least 144 patients (60%), will be eligible for this study. From these eligible patients we expect 108 patients (75%) to give informed consent to participate in the study per year. So, we expect to be able to include 137 patients in 16 months.

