## Replacement of individual subjects after withdrawal

There will be no replacement of individual subjects after withdrawal.

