## Primary study parameter(s)

Scar quality 12 months post-surgery assessed by the observer score of the POSAS scale will be tested for normality before univariate analyses will be performed. If the data are normally distributed, a paired student’s t-test will be used for comparison of the data. Otherwise the Wilcoxon signed-rank test will be applied.

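### A 30% dropout allowance on 105 evaluable patients requires 105/0.7 = 150 enrolled, not 137, and the Summary gives 105 as the number to recruit

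*Protocol*

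**What the plan says.** Section 4.4 of the Protocol takes its effect from a retrospective comparison: "The mean POSAS Observer Score in the hydrosurgery was 14.7 versus 16.7 in the guarded knife group 12 months post-surgery". The spread and the standardised effect are given next: "with a pooled SD of 6.53, resulting in an effect size of 0.3". It adjusts for the within-patient design by "assuming a correlation of 0.4 between POSAS Observer Score within one patient" and concludes: "Given a power of 0.8 and a level of significance of 0.05 a number of 105 patients is needed". Because the primary outcome is measured only at one year, it adds an allowance for loss: "we anticipate on a drop out of 30%, which means we will include 137 patients". The accrual forecast in the same section also uses 137.

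The Summary (Study population) gives a different number: "In total 105 patients will be recruited with a follow-up of 12 months post-surgery".

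Two other places bear on the point. Section 8.5 states: "There will be no replacement of individual subjects after withdrawal". Section 10.1 makes the primary analysis a paired comparison: "If the data are normally distributed, a paired student’s t-test will be used for comparison of the data", with the Wilcoxon signed-rank test otherwise.

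**The concern.** The 105 comes from a power calculation for paired 12-month scores, so it is a number of patients with the outcome observed. Both study areas lie in the same patient, so a patient lost before 12 months removes a complete pair. A 30% dropout is a fraction of those enrolled, so the enrolment target is 105 divided by 0.7. Section 4.4 appears to add 30% of the evaluable number instead, which covers a smaller loss than the one it states.

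The Summary compounds this by giving the evaluable number as the number recruited, with no allowance for loss.

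Two things are at stake. The stated power of 0.8 does not follow from the plan's own dropout assumption. The document also carries two enrolment targets, so it is unclear when recruitment is complete.

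**Working it through.** **Inputs (all from Section 4.4 unless noted).** Means 14.7 and 16.7, difference 2.0; pooled SD 6.53; effect size stated as 0.3 (unrounded 2.0/6.53 = 0.306); within-patient correlation 0.4; power 0.80; significance level 0.05; dropout 30%; enrolment target 137. The Summary gives 105 recruited. Sidedness is not stated; two-sided is assumed and tested below.

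**Step 1: reproduce 105.** The SD of the within-patient difference is 6.53 × √(2 × (1 − 0.4)) = 7.15. The standardised paired effect is dz = d/√1.2, which is 0.274 for d = 0.30 and 0.280 for d = 0.306. The normal approximation is n = (1.960 + 0.842)²/dz².

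- d = 0.30: 7.849/0.075 = 104.65, so 105. The noncentral t gives 107.
- d = 0.306: 101 by the normal approximation, 103 by the noncentral t.
- One-sided 5%: 80 to 84 across the same variants, which does not reproduce 105.

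So 105 is the two-sided paired result, and it counts evaluable pairs.

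**Step 2: reproduce 137.**

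- 105 × (1 + 0.30) = 136.5, rounded up to 137: matches the Protocol.
- 105/(1 − 0.30) = 150: the number that leaves 105 after 30% loss.
- 137 × 0.70 = 95.9, about 96 evaluable, nine short of 105.
- 1 − 105/137 = 23.4%: the largest dropout that 137 can absorb.

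**Step 3: power after 30% loss (two-sided 5%, paired t, correlation 0.4).**

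| Enrolled | Evaluable | Power, d = 0.30 | Power, d = 0.306 |
|---|---|---|---|
| 150 | 105 | 79.4% | 81.0% |
| 137 | 96 | 75.7% | 77.4% |
| 105 (Summary) | 73 to 74 (73.5) | 63.6 to 64.2% | 65.4 to 66.0% |

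**Step 4: check on the approximation that yields 105.** Power is Φ(dz√n − 1.960). At n = 96 this is Φ(2.683 − 1.960) = 76.5% for d = 0.30 and Φ(2.739 − 1.960) = 78.2% for d = 0.306. At n = 105 it is Φ(2.806 − 1.960) = 80.1% and Φ(2.865 − 1.960) = 81.7%. Whichever method is used throughout, moving from 105 to 96 pairs costs between 3.5 and 4 points.

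**Step 5: accrual.** At the Protocol's 108 consenting patients per year, 137 takes 137/108 × 12 = 15.2 months (stated as 16) and 150 takes 150/108 × 12 = 16.7 months. Scaling the stated 16 months instead gives 16 × 150/137 = 17.5 months.

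**The case against.** The arithmetic is hard to dispute; the case on the other side is about weight.

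- **The loss from 137 is modest.** Against the nominal 80%, the shortfall is about 2 to 4 points, depending on the rounding of the effect size and the choice of normal or t calculation. On the t basis with d = 0.30, even 105 evaluable patients give 79.4%, so 150 would not quite reach 80% either. This stands, and the size should be reported that way.
- **The inputs are less certain than that.** The correlation of 0.4 is assumed and the effect comes from a retrospective study. With a correlation of 0.45, 96 pairs would give 79.2% (d = 0.30) or 80.8% (d = 0.306). A lower correlation would reduce power in the same way, so this gives no reason to leave the error in place.
- **The Summary's 105 is probably the evaluable number carried over.** Section 4.4 is the sample size section and uses 137 twice. That is the likely explanation, but the Summary speaks of recruitment, so the two places still conflict. The figure of about 64 to 66% applies only if enrolment really stops at 105 and 30% are then lost.
- **Enrolling 150 is not free.** It means 13 more patients, each undergoing the study biopsies; it could use nearly all of the recruitment window in Section 3; and it may count as a substantial amendment under Section 12.3. This stands, and it favours the wording repair.

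A one-sided reading would put 96 pairs at about 85% power, but it does not reproduce 105 and so does not rescue the text.

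**Conclusion.** The point holds. Section 4.4 presents 137 as the consequence of 30% dropout, and it is not: 137 leaves about 96 evaluable patients, with 75.7 to 77.4% power by the paired t-test (76.5 to 78.2% by the normal approximation). The stated 80% is kept only if dropout is at most about 23%, and with no replacement of withdrawn patients nothing later in the plan makes up the difference. The Summary's recruitment figure contradicts Section 4.4 and, taken literally, would lower power to about 64 to 66% under the same dropout.

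These figures assume a two-sided 5% test, a correlation of 0.4, an effect size of 0.30 to 0.306, and loss of both areas when a patient drops out. The power loss from the 137 error alone is small. The correction is still needed because the stated power and the enrolment target are both wrong as written.

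**What to change.** **Wording only (least costly).** In Section 4.4, keep 137 and state that 30% dropout leaves about 96 evaluable patients and about 76 to 77% power. Alternatively, state that 80% power assumes dropout of no more than 23%. In the Summary, give the same enrolment target as Section 4.4 and label 105 as the number needed with the 12-month primary outcome. Design, endpoint and analysis stay as they are; the only cost is a slightly less favourable power statement.

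**If 105 evaluable patients are to be protected at 30% dropout.** Replace 137 by 105/0.7 = 150 in both sentences of Section 4.4 that use it, update the accrual forecast, and carry 150 into the Summary. This adds 13 patients. By the Protocol's own rates it takes about 16.7 to 17.5 months, which fits the roughly 18 months in Section 3 (dates read as day/month) with little slack. Whether it needs notification as a substantial amendment should be checked against Section 12.3.
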